## Abstract

**Background:**

Hostile anatomy, especially severely angulated neck and tortuous iliac arteries, has always been a conundrum in endovascular aneurysm repair (EVAR). Crossed limb (CL) graft, also called the “ballerina technique,” has been utilized to address this problem by facilitating gate cannulation. In terms of short and long-term outcomes, correlated studies have made inconsistent conclusions and this issue remains controversial. Based on a previous cohort study conducted in our center, we aim to prospectively compare the safety and efficacy between CL and standard limb (SL) configuration in patients receiving EVAR.

**Methods:**

This is a prospective, single-center, non-randomized controlled trial. A total of 275 patients who meet the inclusion criteria will be enrolled and allocated with a 4:11 ratio of CL to SL, which is based on results of our previous study. All patients will receive same perioperative management and postoperative medications. All EVAR procedures will be performed under standard protocol, utilizing Endurant II or IIs Stent Graft. The configuration of the graft stent will be decided by surgeons and confirmed by final angiography. The primary outcome is 3-year freedom from major adverse limb-graft events (MALEs). Endpoints will be assessed at the following time points: 1, 6, 12, 24, and 36 months.

**Discussion:**

To our best knowledge, this crosseD vs. stANdard Configuration in Endovascular Repair (DANCER) trial is the first non-randomized controlled trial to compare these two graft configurations in EVAR. The main aim is to compare the MALEs between two groups at 3 years postoperatively. This trial will hopefully provide high-level evidence for employing CL in EVAR.

**Clinical trial registration:**

[www.chictr.org.cn], identifier [ChiCTR2100053055].

## Introduction

Abdominal aortic aneurysm (AAA) is a pathological, localized dilation of abdominal aorta (1), characterized by decreased smooth muscle cells, extracellular matrix breakdown, inflammatory cell infiltration and endothelial dysfunction (2). The prevalence of AAA increases with age, estimated to be 1.3–1.7% in 65-year-old men (3, 4). Many patients with AAA are asymptomatic and mostly diagnosed after incidental imaging or, in the worst case, rupture (1). With mortality up to 85%, AAA rupture is an important death cause in adults, which renders AAA one of the most important diseases in vascular surgery (5). Both the Society for Vascular Surgery and the European Society for Vascular Surgery have recommended endovascular aneurysm repair (EVAR) as the preferred treatment modality for AAA in certain patients (6, 7). Compared with traditional open surgical repair, EVAR has the advantage of minimal invasiveness and shorter procedure time (8). Nevertheless, EVAR performed in patients with hostile anatomy could be technically challenging and more likely to induce postoperative complications. A large number of studies concluded that hostile proximal neck is associated with a higher rate of type I endoleak, secondary procedure and mortality in the short and long term after the procedure (9–11). Similarly, distal aortoiliac tortuosity has been revealed to be related with higher graft-related complications (12–14). To resolve this problem, great innovations have been made in the past few decades and one of them, crossed limb (CL), was raised in 2002 for patients with severely angulated neck. This ballet-dancer-like configuration could facilitate gate cannulation and theoretically avoid graft disconnection and endoleaks (15). By now, this technology has been widely applied in clinical practice.

For efficacy of the CL in practice, however, related studies have drawn inconsistent conclusions, which makes the true effect of CL doubtful. By analysis of computed fluid dynamics, CL showed a tendency to prevent stent thrombosis, accompanied by tolerance for higher wall shear stress and helicity characteristics (16, 17). On the contrary, long-term fatigue and displacement implications were revealed by the same studies and another one demonstrated that it was the angle of the aneurysm neck other than the configuration that affected hemodynamic index (18). Similar controversial outcomes were observed in clinical trials. Two retrospective cohort trials showed that CL group had a longer procedural time and more type II endoleak compared with standard limb (SL) groups; however, technical success rate, postoperative complications, reintervention and overall survival were comparable (19, 20). This result was mirrored in the latest meta-analysis with no significant difference found in perioperative mortality, endoleak or limb occlusion. This study concluded that CL did not confer inferior clinical outcomes compared to SL in the medium term (21).

To further explore this issue, we conducted a cohort study in 2021, which suggested that no significant evidence was found to favor either configuration in terms of adverse limb events, endoleak, reintervention or overall survival (22). A trend toward a lower risk of type IB endoleak was observed in the CL group after stratification by large aneurysm sac or tortuous iliac artery. On the other hand, CL incurred a higher risk of reintervention and adverse limb events in patients with angulated aneurysmal neck. As commented by editors, our previous study showed interesting results and had the advantage of significant enrolled patients and sufficient time of follow up. However, it was subject to its retrospective, observational nature and other limitations. To elucidate this problem, a prospective study with a uniform reporting standard and careful design is required accordingly (23). Therefore, the utility of CL configuration requires further investigation, which propels us to launch this study.

This prospective, single-center, non-randomized controlled trial aims to compare the safety and efficacy of CL vs. SL configuration in EVAR patients, which could provide high-level evidence for choice of optimal stent graft configuration. The primary outcome of interest is 3-year freedom from major adverse limb-graft events (MALEs).

### Hypothesis to be tested

In AAA patients who receive EVAR, CL is not inferior to SL configuration in terms of safety and efficacy in the short and long term.

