### Outcomes of interest

The primary outcome is 3-year freedom from MALEs, which involves type IB/III endoleak and limb occlusion. Type IB endoleak is defined as persistent direct flow in the aneurysm sac due to inadequate distal seal of the stent graft. Type III endoleak is defined as persistent direct flow resulting from stent graft component separation or fabric tear. Limb occlusion is defined as a total occlusion occurring in limb grafts, regardless of symptoms, or an invasively treated stenosis resulting from thrombus formation (> 50% lumen reduction).

The secondary outcomes involve 3-year freedom from type IA endoleak and 3-year freedom from aortic reintervention. Type IA endoleak is defined as persistent direct flow in the aneurysm sac due to inadequate proximal seal of the stent graft. Aortic reintervention refers to any secondary surgical procedure related to the index EVAR.

Other outcomes consist of three aspects: intraoperative technical outcomes (operation time, radiation exposure time, dosage of contrast medium and technical success rate); short-term postoperative outcomes (length of stay in intensive care unit or vascular ward, acute kidney injury, 30-day overall morbidity, 30-day major adverse cardiac events, 30-day all-cause mortality); long-term outcomes (renal function decline, occurrence of type I/II/III endoleak or stent migration, freedom from major adverse cardiac events, aneurysm related death, overall survival).

Detailed information for outcomes is listed in Table 2.

**TABLE 2 T2:** Detailed information for outcomes.

Outcomes	Definition

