### Sample size calculation

We calculate the sample size for this study based on the results of our previous study (22), in which 11.5 and 7.9% of patients suffered from adverse limb events in CL and SL groups, respectively. In this trial, we hypothesize that the freedom from adverse limb events in the CL group is not inferior to that in the SL group. The predetermined non-inferiority margin on the risk difference scale (δ) is set to 0.15 between the two groups. The type I and II error rates are set to 0.05 and 0.2, respectively. As the intraoperative choice of limb configuration is difficult to randomize, the ratio of enrolled patients between the CL and SL groups is set to 4:11 based on our previous cohort study (22). After accounting for a 20% rate of dropout, it is calculated that 73 subjects are needed for the CL group, and this value is 202 in the SL group. All calculations are performed by PASS 15 software.

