### Statistical analysis

Categorical data is expressed as number and rate, while continuous data is expressed as means ± standard deviation if they are normally distributed or median with interquartile range otherwise. Student’s *t*-test or Mann-Whitney *U*-test is used for univariate analysis of continuous data. χ^2^-test or Fisher’s exact test is used for categorical data. For primary analyses, multivariate logistic regression is used to calculate adjusted odds ratio and 95% confidence interval for short-term outcomes. Cox proportional hazard regression analysis and marginal structural model are adopted to assess the association between limb configuration and time-to-event outcomes.

The propensity score to undergo CL or SL is estimated by logistic regression model based on demographic and anatomic information. Inverse probability of treatment weighting adjusted analyses are performed to achieve weighted balance with standardized differences < 0.10. Sensitivity analysis is conducted to stabilize the weights by truncating the non-overlapping tails of the propensity score distributions which below or above the 1st and 99th percentiles. Subgroup analysis is conducted in terms of large aneurysm sac, severely angulated neck, tortuous iliac arteries and iliac landing zone (whether using bell-bottom iliac stent graft). In addition, this analysis will be carried out in AP and LR subgroups. R studio Version 1.2.1335^1^ and Empower (X&Y solutions, Inc., Boston, MA)^2^ are utilized for statistical analysis.

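### The stated non-inferiority hypothesis covers all safety and efficacy, short and long term, but only adverse limb events have a margin, so the wider claim cannot be established by this design

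*Protocol article*

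**What the plan says.** The protocol article states its hypothesis twice, with different scope. Under Hypothesis to be tested, it is that "CL is not inferior to SL configuration in terms of safety and efficacy in the short and long term"; no outcome is named. Under Sample size calculation it is narrower: "we hypothesize that the freedom from adverse limb events in the CL group is not inferior to that in the SL group". That section also gives the only margin in the document: "The predetermined non-inferiority margin on the risk difference scale (δ) is set to 0.15 between the two groups".

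Under Outcomes of interest, the primary outcome is freedom from MALEs at 3 years. Beyond it, "The secondary outcomes involve 3-year freedom from type IA endoleak and 3-year freedom from aortic reintervention". The other outcomes include acute kidney injury and 30-day morbidity, cardiac events and mortality. None of these has a margin.

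Under Statistical analysis, "multivariate logistic regression is used to calculate adjusted odds ratio and 95% confidence interval for short-term outcomes". Time-to-event outcomes go to Cox regression and a marginal structural model, described as assessing association. Univariate comparisons use t, Mann-Whitney, chi-square or Fisher tests. No non-inferiority criterion appears in that section.

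**The concern.** Non-inferiority is shown by excluding a prespecified amount of harm. Where no amount is specified, neither a test of no difference nor a confidence interval can show it, because there is nothing for the interval to exclude. The hypothesis therefore promises conclusions on short-term safety, type IA endoleak and reintervention that the design has no means of reaching. The short-term part is the most exposed, since the one outcome with a margin is assessed at 3 years.

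What is at stake is the final claim. The trial is presented as high-level evidence for choosing a configuration. With 73 CL patients, an uncommon harm could be doubled and still give a non-significant result. Reintervention deserves particular care: the Introduction reports that the previous cohort at this center saw a higher reintervention risk with CL in angulated necks.

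**Working it through.** **1. The plan's own figure.** Inputs, all from Sample size calculation: "11.5 and 7.9% of patients suffered from adverse limb events in CL and SL groups, respectively" (freedom 0.885 and 0.921), margin 0.15, error rates 0.05 and 0.2, ratio 4:11, dropout 20%. With unpooled variance and a one-sided 0.05 level:

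n(SL) = [0.921×0.079 + 0.885×0.115/(4/11)] × (1.645 + 0.842)² / (0.15 − 0.036)² = 167.8, so 168; n(CL) = 167.8 × 4/11 = 61.

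Multiplying by 1.2 gives 201.6 and 73.2, which reproduces the stated 202 and 73. Every event-rate and margin input concerns limb events. No other outcome enters the sizing.

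**2. Scope set side by side.**

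| Part of the hypothesis | Margin | Planned analysis |
|---|---|---|
| Limb events, 3 years | 0.15 risk difference | Cox, marginal structural model |
| Type IA endoleak and reintervention, 3 years | none | Cox, marginal structural model |
| Kidney injury, 30-day morbidity, cardiac events, mortality | none | logistic odds ratio with 95% interval |

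**3. What a non-significant result would be worth.** The article gives no event rates for the outcomes without a margin, so the SL risks below are assumptions. Group sizes are those enrolled (73 and 202) and those left after 20% dropout (73×0.8 = 58; 202×0.8 = 162). The question is how often a two-sided 5% Pearson test misses a true doubling of risk under CL. The results come from exact enumeration over two binomials, counting rejections in the direction of harm.

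| Assumed SL risk | CL risk | Missed, 73/202 | Missed, 58/162 |
|---|---|---|---|
| 2% | 4% | 82% | 84% |
| 5% | 10% | 66% | 71% |
| 10% | 20% | 42% | 48% |
| 20% | 40% | 9% | 16% |

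Hand check of the 5% row at 73/202 by normal approximation. Pooled risk = (7.3 + 10.1)/275 = 0.0633. Null standard error = √[0.0633×0.9367×(1/73 + 1/202)] = 0.0332. Alternative standard error = √(0.09/73 + 0.0475/202) = 0.0383. Power = Φ[(0.05 − 1.96×0.0332)/0.0383] = Φ(−0.40) = 0.35, so about 65% is missed.

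By the same approximation the miss rate is 50% at an SL risk of 8.1% (73/202) or 9.9% (58/162). For a doubled hazard by the Schoenfeld formula it is 50% at about 12% or 15%.

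**4. What an interval would leave open.** If both groups showed the same risk p at 73/202, the upper 95% limit of the odds ratio would be about exp{1.96×√[(1/73 + 1/202)/(p(1−p))]}: 6.8 at p = 2% and 3.4 at p = 5%.

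**5. Continuous outcomes.** Power for a 0.5 SD difference is about 96% at 73/202 and 90% at 58/162, so the figures in step 3 do not carry over to operation time, contrast dose and the like.

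These calculations are unadjusted. Inverse probability weighting would be expected to lower the effective sample size further.

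**The case against.** The strongest reply is that the article narrows its own hypothesis. The sample size section speaks of limb events, one primary outcome is named throughout, and everything else is labelled secondary or other. Sizing a trial on the primary outcome alone is normal, and the interpretation of secondary outcomes is commonly left to a statistical analysis plan, which is not shown here. That is fair, and the absence of margins for secondary outcomes would not be a fault by itself. What remains is that the sentence headed as the hypothesis to be tested still claims more than the design can test.

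Three stronger readings are tempting, and the documents do not support them:

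- A reader might infer that the trial will declare non-inferiority wherever p exceeds 0.05. No section says so, and 95% confidence intervals are already planned for short-term outcomes.
- A reader might take the Introduction's account of a meta-analysis, which moves from no significant difference to not inferior, as the sponsor's own reasoning. It reports the conclusion of that cited study. The sponsor describes its own cohort neutrally and calls the effect of CL doubtful.
- A reader might conclude that a doubled harm is missed half the time or more for every other outcome. That holds only for binary outcomes with SL risk up to roughly 8–10%. 30-day morbidity is a broad composite whose rate is not given and may well be higher.

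The reintervention signal in the previous cohort was confined to angulated necks, and a subgroup analysis for severely angulated necks is planned. That subgroup has no margin either, and it is smaller than the whole trial.

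**Conclusion.** The concern holds as a mismatch of scope. The hypothesis as worded cannot be established beyond limb events, and its short-term part has no margin at all. The plan does not commit to reading non-significance as non-inferiority, but it gives no other path to the wider claim.

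The size depends on event rates that the article does not state. For uncommon binary outcomes (assumed SL risk 2–5%) a doubling would be missed in about two thirds to five sixths of trials. At 10% it would be missed a little under half the time, and at 20% seldom. The sample size, the margin and the limb-event hypothesis are untouched by this point.

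**What to change.** Under Hypothesis to be tested, restrict the claim to the outcome that has a margin: CL is not inferior to SL in 3-year freedom from MALEs. This brings it into line with the limb-event hypothesis under Sample size calculation.

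Under Statistical analysis, add that secondary and other outcomes are reported as adjusted estimates with 95% confidence intervals, and that non-inferiority will not be claimed for them on the basis of a non-significant result.

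This is a change of wording only, with no further patients or data. The cost is a narrower headline: non-inferiority for limb events, with other safety and efficacy outcomes described by estimates.

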## Materials and methods

### Study design and approvals

This study is a prospective, single-center, non-randomized controlled study conducted in West China Hospital. This protocol is developed according to Standard Protocol Items: Recommendations for Interventional Trials (SPIRIT) 2013 Statement for study protocols of clinical trials (24). The SPIRIT checklist has been completed in additional file 1.

### Recruitment and enrollment

We recruit patients diagnosed with infrarenal AAA (Figure 1) from 1st December 2021. The eligibility criteria for inclusion and exclusion are shown in Table 1. Adult patients with indicated infrarenal AAA (diagnosed with ICD I71.3 and I71.4) and suitable iliofemoral anatomy are included in our study. Excluded are patients who could not tolerate perioperative medications and patients expected to receive reintervention. Both groups of patients share general inclusion or exclusion criteria.

**FIGURE 1 F1:**
[figure not shown]
The procedure of screening, randomization and follow-up in the DANCER trial.

**TABLE 1 T1:** Inclusion and exclusion criteria for participants.

Inclusion	Exclusion
Patients are considered eligible if they meet all of the following criteria: 1. Men or non-pregnant women aged ≥ 18 years and with sufficient life expectancy to complete all the processes of the study. 2. Diagnosed with infrarenal abdominal aortic aneurysm (according to ICD I71.3 and I71.4) and indicated for surgical intervention. 3. Local anatomy of bilateral femoral and iliac arteries allows for guide wire passing. 4. Provide written informed consent and agree to participate in the study. 5. Placement of iliac endografts is required during the procedure.	Patients shall be excluded from the trial if they meet any of the following criteria: 1. Unable to tolerate contrast agents, antiplatelets or anticoagulants. 2. Recorded with previous primary repair for AAA, no matter EVAR or open surgical repair.

AAA, abdominal aortic aneurysm; EVAR, endovascular aneurysm repair.

We will recruit patients by putting up posters and advertising online to meet the expected enrollment. In addition, we provide fast-track follow-up for patients who are willing to participate in our study. Figure 2 shows the schedule of enrollment, interventions and assessments, following the template provided by SPIRIT (24).

**FIGURE 2 F2:**
[figure not shown]
The schedule of enrollment, interventions and assessments.

### Allocations of intervention

Based on the anatomic features of the aneurysm by intraoperative imaging, surgeons will determine whether to adopt CL or SL configuration. When both configurations are feasible, surgeons will assign the limb configuration based on covariate adaptive matching between the two groups. The major matched covariates are as follows: age, gender and aneurysm diameter. Both surgeons and participants are not blinded to the interventions, and only statisticians who analyze the data are blinded.

The CL and SL configurations are defined as crossed or uncrossed limb grafts in anteroposterior view of the final angiogram, respectively. CL is further subdivided into anterior-posterior (AP) cross and left-right (LR) cross, which correspond to ≥ 50 and < 50% overlapped areas between two limb grafts in the angiogram. SL is similarly subdivided into AP parallel and LR parallel with the same definition.

The included patients will receive the same perioperative management, including blood pressure control, analgesia and medication with antiplatelets and statins. In interventional operating room, both common femoral arteries will be used for percutaneous or cut down access. After administration of 0.5 mg/kg unfractionated heparin, graft stents are placed in accordance with instruction for use by an experienced surgeon of vascular surgery. Treatment procedures are performed under a standard protocol. The Endurant II or IIs Stent Graft (Medtronic, Minneapolis, Minn) is used for repair.

Postoperative medications include antiplatelet monotherapy (aspirin 100 mg once a day or clopidogrel 75 mg once a day) and statins. Patients are expected to take these medications all life unless severe adverse event occurs. Anticoagulants, such as low molecular weight heparin or direct oral anticoagulants, will be used according to surgeons’ decision.

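### Unblinded surgeons both judge whether either configuration is feasible and make the covariate-adaptive assignment, so it can be foreseen or avoided; the randomization caption and the 4:11 wording also need correcting

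*Protocol article*

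**What the plan says.** The operative text is in Allocations of intervention and has two steps. First: "Based on the anatomic features of the aneurysm by intraoperative imaging, surgeons will determine whether to adopt CL or SL configuration". Second: "When both configurations are feasible, surgeons will assign the limb configuration based on covariate adaptive matching between the two groups". The covariates follow: "The major matched covariates are as follows: age, gender and aneurysm diameter". The same paragraph says that surgeons and participants know the configuration and that only the analysing statisticians are blinded. The next paragraph defines the two groups by what the final angiogram shows.

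Other places describe the same process differently:

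- Abstract, Methods: patients "will be enrolled and allocated with a 4:11 ratio of CL to SL", and later "The configuration of the graft stent will be decided by surgeons and confirmed by final angiography".
- Sample size calculation, where 4:11 is taken from the earlier cohort: "As the intraoperative choice of limb configuration is difficult to randomize, the ratio of enrolled patients between the CL and SL groups is set to" that value.
- Study design and approvals: "This study is a prospective, single-center, non-randomized controlled study conducted in West China Hospital".
- Figure 1 caption: "The procedure of screening, randomization and follow-up in the DANCER trial".

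Statistical analysis estimates a propensity score from demographic and anatomic information and applies inverse probability of treatment weighting.

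**The concern.** Patients for whom both configurations are feasible are the one part of this trial in which assignment could be independent of the surgeon's view of the case. As written, the rule gives that up, because the person with the opinion controls both entry to this stratum and the arm given within it. If surgeons hold back one configuration from cases that look difficult in ways nobody records, the comparison carries that preference into the primary outcome. In a non-inferiority trial such a bias could hide a real disadvantage of CL or create a false one. The caption and the ratio wording are lesser matters, but they leave the reader unsure what kind of allocation took place.

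**Working it through.** **1. Who controls each step (Allocations of intervention).**

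| Step | Decided by | Safeguard stated |
|---|---|---|
| Is only one configuration feasible, or both? | Surgeon, during the operation | None |
| If both, which one? | Surgeon, by adaptive matching on three covariates | None: no random element, no independent source |
| Which group is the patient counted in? | Final angiogram | Not applicable |

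Matching without a random element is a fixed function of the new patient's covariates and those of patients already treated. Whoever applies it knows the result. Because feasibility is judged by the same surgeons, an unwelcome result can be avoided by classing the patient as suitable for one configuration only.

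**2. What the weighting can and cannot remove.** Data collection lists neck length and angulation, sac diameter, thrombus load, iliac tortuosity and distal calcification, among others. The propensity score can use these, so measured anatomy is addressed. The Discussion says the choice also depends on surgeons' experience, which the described score does not include.

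Suppose that, at given measured covariates, an unrecorded trait raises event risk by d and is present in a fraction p1 of CL patients and p0 of SL patients. The bias left in the risk difference after weighting is

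bias = d × (p1 − p0).

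The document gives none of d, p1 or p0, nor the share of patients suitable for both. Either sign is possible, so no figure can be put on the bias. For scale, the planned difference is 11.5% − 7.9% = 3.6 points against a margin of 15 points, which leaves 11.4 points.

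**3. The 4:11 ratio.** The plan's own sample size comes first. Inputs from Sample size calculation: freedom from events 0.885 (CL) and 0.921 (SL), margin 0.15, type I error 0.05 (taken as one-sided), power 80%, ratio 4/11. With unpooled variance:

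- n(SL) = (1.645 + 0.842)² × [0.921 × 0.079 + 0.885 × 0.115 / (4/11)] / (0.15 − 0.036)² = 168 after rounding up
- n(CL) = 168 × 4/11 = 61
- multiplied by 1.2 for dropout: 201.6 and 73.2, that is 202 and 73, total 275, as stated.

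Let f be the share suitable for CL only, e the share suitable for both, and s the share of the latter given CL. The overall CL share is f + e × s. Only s is under the trial's control; f and e emerge in the operating room. The planned share, 4/15 = 26.7%, is therefore an expectation.

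Power at other shares, with 219 evaluable patients (58 + 161 after 20% loss), the same rates and one-sided 0.05, is the normal probability below 0.114/SE − 1.645:

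| CL share | CL / SL | Power |
|---|---|---|
| 15% | 33 / 186 | 61% |
| 20% | 44 / 175 | 70% |
| 26.7% (planned) | 58 / 161 | 78% |
| 35% | 77 / 142 | 85% |
| 50% | 110 / 109 | 89% |

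Shares other than 26.7% are assumptions. The table ignores any loss from weighting. It concerns precision only and says nothing about the bias in step 2.

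**4. The caption.** Abstract, Study design and approvals, and the limitations in the Discussion all call the trial non-randomized, and Sample size calculation says why. A randomization step in the Figure 1 caption cannot stand beside them.

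**The case against.** A reader might infer that the article gives several incompatible allocation rules. It does not go that far. Anatomy first and matching second is a sequence. The abstract's statement that surgeons decide condenses it, since surgeons act in both steps. Sample size calculation presents 4:11 as a planning ratio drawn from the earlier cohort, and no section calls it a quota. Only the caption plainly conflicts, and it may be template wording.

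A reader might also infer that patients suitable for both would receive CL at very different rates under a 4:11 quota and under 1:1 matching. The article states no matching ratio, adaptive methods can target unequal ratios, and the feasibility shares are not given. No such gap can be derived.

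It is also fair to say that the article does not state who keeps the covariate totals, and that the full protocol may add operating detail. The Discussion acknowledges selection bias and lists non-randomization as a limitation, and a main driver of choice, anatomy, is measured and enters the weighting. It would be too strong to say that the result merely reflects who was steered to CL.

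What remains is stated, not omitted: surgeons assign, surgeons are unblinded, and surgeons judge feasibility. A matching rule has to be applied by someone with the totals or their result, and the article names the surgeon as the one who assigns.

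**Conclusion.** The point holds as a weakness in a stated rule and should be corrected. The assignment of patients suitable for both configurations can be foreseen or avoided by the person treating them, and weighting on recorded data cannot undo selection on unrecorded impressions. Neither the size nor the direction of the bias can be computed from the document, and the document does not show that steering will occur.

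The caption is an error of wording. The abstract's 4:11 is loose wording for a ratio that no stated rule can guarantee. If the CL share drifts from 26.7%, the consequence is for power, about 61% to 89% over assumed shares of 15% to 50%, under one-sided 0.05 and the plan's event rates.

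**What to change.** 1. Reconcile the abstract, the Figure 1 caption, Allocations of intervention and Sample size calculation into one description. Correct the caption, and call 4:11 the expected planning ratio and not a quota.
2. Have the surgeon record feasibility (both, CL only, or SL only) before any assignment is known. The judgement itself stays with the surgeon and is unchanged.
3. For patients recorded as suitable for both, obtain the assignment from a covariate-adaptive program run outside the surgical team. A random element is preferable because it stops the next assignment being foreseen. It is optional because it touches the declared design; if it is added, the design label and consent wording must match.

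The cost is protocol wording, one data field, a small program and a short query during the procedure. The matching already requires covariate totals. The downside is that the final CL:SL ratio may depart from 4:11, which the present rule does not prevent either.
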